### Data collection and management

All data collected in this trial will be recorded on standardized paper case report forms (CRF). The sponsor-investigator (AS) is responsible for ensuring that all parts of the CRFs are filled in correctly. The two used questionnaires, SANE score [22] and the PRTEE score [25], are commonly used validated tools. The principal investigator is responsible for ensuring that all parts of CRFs are filled in correctly. Any change or correction to the CRF should be dated and initialed. Each CRF must be signed at least once by the investigator.

The physician closely supervises the participants during rehabilitation visits in order to improve their compliance to the rehabilitation program (CF above). In case of missed appointment, a new date will be proposed by phone. If participants deviate from protocol, the remaining follow-up visits will still be performed and the corresponding data will be collected.

All protocol-required information collected during the trial must be entered by the sponsor-investigator, or designated co-investigator, in the CRF. The CRF pages should be completed and signed the same day that a trial subject is seen for any of the trial procedures. For all CRFs, a copy is immediately stored on the digital secured server of the principal investigator. In order to ensure that the database reproduces the CRFs correctly, the sponsor-investigator, or designated representative, will perform a double entry of the data on two distinct CSV files. For each visit, a different CSV file will be created. Then, the CSV files will be compiled on a database using “R” software (R Foundation for Statistical Computing, Vienna, Austria). The quality of the data entered is guaranteed using “R” software as follows: (i) the duplicate CSV for double entry are digitally compared, and discordant results identified, and (ii) the completeness, validity, and plausibility of the data will be tested for each variable. In case of discordant data, the principal investigator will clarify or correct the problematic data. All eventual changes will be recorded. If no further corrections have to be made in the database, the latter will be closed and used for statistical analyses. All important trial documents (e.g., CRFs) will be archived for at least 10 years after completion of the clinical trial.

Trial data of the patient will be stored in a coded manner. The names of the patients will not be disclosed on CRF. A sequential unique patient number will be attributed to each patient into the trial and reported on the CRF. Identification of patients must be guaranteed at the center. Identification of the patients will be stored on a sequential list stored in the principal investigator’s secured server. The principal investigator and designated representatives will have access to the coded dataset and the identification list during, at the end, and after the study.

Note: in order to insure the blinding of the principal investigator, the allocation list will only be accessible to the co-investigator (MF), or under request to the informatics crew for backup.

### Oversight and monitoring

[name] (CB), chief physician of the Physical Medicine & Rehabilitation Department of the Lausanne University Hospital, will monitor this study, as follows: (i) At the beginning of the study, he will ensure that the randomization and blinding procedure will be respected, first with a sham patient. He will then monitor the first injection procedure for the first patient and ensure that the concealment of allocation is respected. (ii) The first 3 months, then every 3 months, he will ensure that consent forms and CRF are correctly fulfilled and stored. He therefore also ensures that all data are available for the final data analysis. (iii) All kinds of adverse events must be transmitted to him. He will manage or supervise reporting of adverse events and follow-up of concerned patients. (iv) He will be advised of all withdrawals or discontinuations of patients. (v) He will verify the reliability of the statistical analysis. (vi) If deemed necessary, he will plan additional monitoring visits for either the intervention or the data collection.

Adverse events and serious adverse events are recorded in the CRF. Serious adverse events are recorded in dedicated forms and reported to the ethical committee within 7 days. Adverse reactions or suspected unexpected serious adverse reactions are recorded in dedicated forms and reported to the ethical committee within 7 days.

Regular audits are not intended. For the purpose of onsite inspection or audit, the competent authorities or ethics committee may require access to all source documents, CRF, and other trial-related records. The principal investigator must ensure availability of these documents and support the work at any time.

## Discussion

The presented study design allows the investigators to assess the usefulness of PRP as adjuvant therapy to ECRB needling in case of tennis elbow with a randomized controlled trial and to evaluate the effectiveness of a comprehensive integrative rehabilitation protocol. The main indication for infiltrative therapy for epicondylitis is the failure of the first-line treatment. To the best of our knowledge, the most efficient infiltrative procedure consists of tendon fenestration. Whether PRP should be added or not during the tendon fenestration remains debated. There are virtually no contraindications for tendon fenestration and PRP in case of epicondylitis.

In the most recent meta-analysis focused on the management of tendinopathies, PRP was reported to be beneficial compared to others infiltrative therapies [12, 25, 26]. Many of the studies included comparisons between PRP and corticosteroids [7, 27-30]. Given that corticosteroid infiltrations have been shown to be deleterious for epicondylitis [5], the authors considered that the potential observed PRP benefits reported in recent meta-analyses including corticosteroids in control group [12, 25, 26] should not support the use of the PRP itself in clinical practice. Rather, the efficacy of PRP in addition to tendon fenestration compared to tendon fenestration alone remains controversial. Martin et al. [14] found in a partially blinded randomized controlled trial (RCT) involving 71 patients no clinical differences at 6 months of follow-up between 2 sessions of fenestration with either saline + local anesthetic or PRP + local anesthetic. In a similar blinded RCT involving 50 patients, Schöffl et al. [15] found no clinical differences at 6 months of follow-up. Montalvan et al. [16] found in an RCT involving 50 patients no clinical differences at 6 months of follow-up between 2 infiltrations of PRP and saline solutions. Rehabilitation was not allowed during the trial and the tendon was not fenestrated. Mishra et al. [17] reported in a blinded RCT involving 119 patients a positive clinical effect of PRP over saline solution, using a single injection with fenestration. Behera et al. [18] found similar results in a small RCT on 25 patients.

The main strength of the present study design is the case series preceding the RCT. First, it allows to study the effectiveness of combined rehabilitative therapies on symptoms relapse, as well as to standardize the studied population for the RCT. Second and most important, the studied population for the RCT will be better standardized (i.e., all patients with epicondylitis refractory to the same first-line therapies program). The reproducibility of the results will therefore be strengthened. Finally, publishing both the case series and the RCT together will help establishing a comprehensive complete management of the pathology, and giving clinical recommendations in case of positive outcomes. On the other hand, in case of suboptimal clinical outcomes, the presented study design could be reworked in a future trial.

The first main limitation is the small minimum sample size for the RCT (58 patients), chosen to detect a pain improvement difference of 10% between groups. Indeed, in case of success of the rehabilitation protocol, not more than 58 patients will be randomized. It could even be necessary to increase the initial sample size of 232 patients during the study. This small sample size of 58 patients might be prone to sampling variability, reason why stratification is planned. Authors consider that detecting a difference between groups smaller than 10% is not relevant, because the use of PRP should be supported by differences that are clinically relevant rather than statistically significant. PRP is considered as a safe treatment, widely used in sports medicine and promoted by medical companies. Financial interest might therefore easily influence the therapeutic decisions, even if the PRP cost-effectiveness has never been clearly demonstrated for tendon use [26–28]. The second main limitation concerns the inherent variability of the rehabilitation protocol. Indeed, like in virtually all case series with a rehabilitation protocol that include different items, the patient’s implication can differ. Moreover, it is difficult to apply the ESWT therapy with a strict standardized protocol for different reasons. First, because the benefits of ESWT treatment can be achieved after a variable amount of time, the rehabilitation length before the intervention varies between 3 and 6 months. Second, the tolerability and energy delivered can differ between patients. Finally, because the rehabilitation protocol including ESWT is applied to all patients, it is not possible to differentiate the effect of ESWT from other items of the rehabilitation.

The results of this study will provide insights into the effect of PRP as adjuvant therapy to tendon fenestration and may help identifying the best preceding and concomitant rehabilitation protocol.

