## Background

The conservative management of lateral epicondylitis is known to be a difficult-to-treat annoying condition. The first-line conservative management includes physical therapies, orthotics [1], and extracorporeal shock wave therapy (ESWT) [2]. The success rate of ESWT for lateral epicondylitis depends mainly on the protocol that is followed. For instance, poor results have been observed with too low energy [3]. Focused ESWT has been showed to be as effective as surgical tenotomy [4].

Infiltrative therapies might be proposed in case of persistent symptoms. It has been well established that corticosteroids are efficient in the short-term but deleterious in the long-term [5, 6] likely for degenerative purposes [7]. Prolotherapy, autologous blood or botulinic toxin injections, and others infiltrative therapies are less studied and are therefore not clearly supported by the current literature [8–10]. Stem cells might be an appropriate alternative in the future [11].

Platelet-rich-plasma (PRP) is nowadays widely used for tendinopathies, considered as safe, and currently supported by the strongest scientific journals [12]. However, the potential benefits of PRP are discordant, especially concerning the elbow. Even if the superiority of PRP over corticosteroids is well established [13], the efficacy of PRP in addition to tendon needling or fenestration compared to tendon needling or fenestration alone is still controversial [14–19].

Several factors have been advocated to influence PRP outcomes. The most relevant ones are direct mechanical action of the needle and fenestration technique, number of PRP injections, cell counts (platelets, white blood and red blood cells), activation of the platelets, concomitant local anesthetic use, peri-interventional use of NSAIDs and corticosteroids, concomitant rehabilitation, or a contrario immobilization [20]. The positive results observed in the previous reported studies remain debatable as they can be [17, 18] related to either PRP, fenestration [21], or any of the abovementioned confounding factors.

The first aim of this study is to determine the proportion of patients that would need an infiltrative technique after a proper rehabilitation protocol including physical therapies, focused ESWT, and orthotics and Kinesio taping for all patients. Our second aim is to establish whether PRP as adjuvant therapy to fenestration would increase clinical outcomes.

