### Study design

This study will include 232 patients and will be conducted in two steps (Fig. 1). The first step consists in an observational case series. During this step, all patients will benefit from a proper rehabilitation including epicondylar stretching and eccentric strengthening; periscapular and global tonification; postural adjustment; manual therapies including trigger points release, epicondylar taping, or bracing; and focused shockwave therapy (Additional file 1). The second step consists in a case-control superiority trial randomized 1:1 between PRP (intervention group) and saline (control group) injections. A stratification is planned on age and lesion pattern.

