### Study treatments and interventions

All patients should perform the rehabilitation protocol during the 3 months following the intervention (Additional file 1). During this protocol, all patients will perform global and specific active strengthening and self-stretching, focused ESWT, focused therapies, Kinesio taping, and orthotics. After 3 months, if a constant but insufficient symptom alleviation is observed, the rehabilitation program could be lengthened by 3 months (i.e., rehabilitation months 4–6). If a radiological ECRB lesion persists on ultrasonography, shockwave therapy will be performed during rehabilitation months 4–6. If the rehabilitation protocol enables symptom disappearance (i.e., the rehabilitation was successful), the intervention will not be performed. If, for any other reason, the intervention cannot be performed, the patient will be dropped out of the study.

It is not clear whether PRP should be used or not as an adjuvant procedure to tendon needling. An injection of saline solution during the procedure as comparator seems the most logical, because it (i) allows a proper blinding of both patient and physician, (ii) has no deleterious effects on tendon repair (contrary to active products such as corticosteroids) and therefore no influence on clinical outcomes, and (iii) has no potential side effects.

In both groups, the intervention will occur under strict aseptic conditions as following: First, a local anesthetic blockade of the radial nerve under the arcade of Frohse will be performed under ultrasonographic control. Then, an ultrasound-guided needling of the ECRB tendon will be performed, using the fenestration technique: 25 repetitions with a 20-gauge needle. During the procedure, the lesion will be fulfilled with either PRP (experimental group) or saline solution (control group). The PRP (ACP Arthrex) will be prepared using a double syringe system under the manufacturer’s recommendation. From 15 ml of peripheral blood, the PRP will be extracted on site using centrifugation (1500 rpm 5 min), as recommended by the manufacturer. After the intervention, the learned self-exercises should be continued as long as necessary. The use of ice and pain medication with paracetamol or opioids (tramadol, codeine) will be used to manage pain, if necessary.

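### The rehabilitation step has no comparator, so it can describe outcomes under the programme but cannot show its efficacy or help identify the best rehabilitation protocol

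*Protocol article*

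**What the plan says.** All references are to the protocol article.

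**What is claimed for rehabilitation**
- The Aims section lists four aims. The last two are the efficacy of first-line rehabilitation, first clinically and then on tendon repair. Neither is hedged.
- The Discussion opens by saying that the design allows the investigators "to evaluate the effectiveness of a comprehensive integrative rehabilitation protocol". Its paragraph on the main strength again uses the word effectiveness for the combined rehabilitative therapies.
- The closing sentence of the Discussion says that the results "may help identifying the best preceding and concomitant rehabilitation protocol". The Discussion paragraph of the Abstract says nearly the same.
- The Background words the aim differently: "The first aim of this study is to determine the proportion of patients that would need an infiltrative technique after a proper rehabilitation protocol".

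**What is done**
- Study design: "The first step consists in an observational case series. During this step, all patients will benefit from a proper rehabilitation". The second step is a "case-control superiority trial randomized 1:1 between PRP (intervention group) and saline (control group) injections".
- Study treatments and interventions: "All patients should perform the rehabilitation protocol during the 3 months following the intervention". The programme before needling may be lengthened from 3 to 6 months in patients who are improving steadily but not enough.
- Outcome measurements and assessments: the rehabilitation endpoints are the proportion of patients who do not need needling, and clinical and ultrasound measures that include months −3 and 0.
- Statistical analysis: the tests described compare the treatment and control groups of the randomised step.

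**What is conceded**
- The limitations say that the effect of shock waves cannot be separated from the other components, because all patients get the programme. They do not say that the effect of the whole programme cannot be separated from recovery without it.

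**The concern.** Efficacy and effectiveness are causal words. They refer to the difference between what happens with the programme and what would have happened without it. A single treated group supplies only the first of these. Over 3 to 6 months, three other things can move the same endpoints: natural recovery, regression to the mean in patients who come for care when symptoms are bad, and the expectations of patients who know they are being treated.

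The word best needs more still: at least two protocols and a fair comparison between them. The design has one protocol.

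Two of the four listed aims, and half of the closing sentence, therefore claim something that the design cannot deliver. This matters for reporting, because the Discussion foresees clinical recommendations for the whole management pathway if outcomes are positive. A success proportion read as a treatment effect could feed into those recommendations.

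**Working it through.** **Step 1. Reproduce the planned numbers and see what they are sized for.** Inputs from Sample size: difference 10, SD 10, power 95%, significance level 5% (taken as two-sided), dropout 10%, rehabilitation success 75%.

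- Per arm: n = 2 × (1.960 + 1.645)² × (10/10)² = 2 × 12.996 = 25.99, rounded up to 26; total 52.
- Dropout: 52 / (1 − 0.10) = 57.8, rounded up to 58.
- Enrolment: 58 / (1 − 0.75) = 232.

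Both stated figures reproduce exactly. They are sized for PRP versus saline. The 75% enters only as a recruitment multiplier; no contrast involving rehabilitation is sized.

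**Step 2. What step 1 can estimate.** At 75% success, 0.75 × 232 = 174 patients succeed. The Wilson 95% interval for 174/232 is 69.1% to 80.1%. As a description of what happens to patients on this programme, that is a good estimate.

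**Step 3. What step 1 cannot estimate.** Let r be the percentage who would have reached the same state over the same period without the programme. The part due to the programme is 75 − r. The documents give no value for r, so the values below are assumptions that show the range.

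| Assumed r | Part due to the programme |
|---|---|
| 20% | 55 points |
| 40% | 35 points |
| 60% | 15 points |
| 75% | 0 points |

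All four rows produce the same observed 75%. More patients would narrow the interval in Step 2 but would not help to choose between the rows. The table is not evidence about the size of any bias; it shows only that the quantity is not identified. The same reasoning applies to changes in pain, function, grip and ultrasound from the start of rehabilitation to month 0.

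**Step 4. Is any rehabilitation protocol compared with another?**
- Before needling: no. All patients receive the programme.
- Around and after needling: no. The sentence on rehabilitation after the intervention covers all patients. It stands in a paragraph that goes on to describe the period before needling, so its timing could be read either way. On both readings nothing differs by arm.
- Variation within the programme: length (3 or 6 months), shock-wave energy and patient involvement do differ. Length follows the patient's response, energy follows tolerance, and involvement is the patient's own. None is allocated, so comparing patients on these features would compare different kinds of patient.

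**Step 5. Does the stated limitation cover the gap?** It argues that because everyone gets the programme, one component cannot be isolated. The same premise means that the programme as a whole cannot be isolated from no programme, but that step is not taken. The closing sentence on the best protocol then follows directly and sits badly with the concession.

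**The case against.** The best case for the article is that it is mostly candid. It calls step 1 an observational case series, the Background states the aim as a proportion, and the first-listed secondary endpoint is that proportion. The closing sentence is hedged in both places, and no test or decision rule hangs on it. The limitations admit part of the problem. All of this is right, and it keeps the point to one of wording. It does not remove it: aims 3 and 4 and the effectiveness statements in the Discussion carry no hedge, and no analysis plan can supply a comparator that the design lacks.

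A reader might be tempted to go further. The documents do not support these stronger readings:
- *The whole closing conclusion fails.* Its first half concerns PRP added to fenestration, which the randomised comparison addresses. Only the second half is affected.
- *The article promises to find the best protocol.* It says only that the results may help.
- *The 75% will be reported as efficacy.* In the article 75% is a planning assumption, and no test of rehabilitation efficacy is planned.
- *Patients with recent onset inflate the success rate.* The listed entry criteria set no symptom duration, but the actual mix is unknown.
- *Step 1 outcomes are rated by the unblinded physician who gives the shock waves.* Pain VAS, SANE and PRTEE are patient ratings and grip is measured; ultrasound is the main rater-dependent outcome. What does stand is that patients know what treatment they receive.

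One further caution: the only change that the outcome section defines outright is post-intervention against month 0. Change from the start of rehabilitation to month 0 is a reasonable reading of the −3 and 0 month assessments and of the rehabilitation efficacy row in Table 1, but it is not spelled out.

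**Conclusion.** The point holds in this form. The efficacy wording of aims 3 and 4, the effectiveness wording in two places in the Discussion, and the best-protocol clause in the Abstract and Discussion claim more than a single-group case series can support. The size of the gap cannot be given as a number: with 75% success, the part due to the programme could be anything from 55 points to none across the assumed range of 20% to 75% recovery without it. The conclusion itself rests on none of these values, only on the absence of a comparator, which the article states.

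The descriptive aim in the Background, the precision of the success proportion, the sample size, and the randomised PRP versus saline comparison are untouched. This is a correction to what the trial may conclude from step 1, not a flaw in its primary analysis.

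**What to change.** Wording changes, which can be made while the trial runs:

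1. **Aims 3 and 4:** restate them in the descriptive form already used in the Background. The aims become to describe the proportion of patients not needing needling after the programme, with a 95% confidence interval, and the change in clinical and ultrasound outcomes during it.
2. **Discussion, opening paragraph and main-strength paragraph:** replace effectiveness with the same descriptive wording.
3. **Abstract and end of the Discussion:** delete the clause on the best preceding and concomitant rehabilitation protocol. Keep the half of the sentence that concerns PRP.
4. **Limitations:** add that, without a comparator, the effect of the whole programme cannot be separated from natural recovery.

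The cost is a weaker claim for step 1. No change to design, recruitment, data collection or the randomised analysis is needed.
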